### 2.2. Participants

The participants were recruited in the central area of Portugal, more specifically in the region of Sertã. The sample was recruited by the non-probabilistic method for convenience. One hundred and fifty individuals from the community were personally invited, but only 102 agreed to participate in the study (mean age of 72.32 ± 5.2 and BMI 29.47 ± 4.85). Participants will be selected according to the following inclusion criteria: individual of both genders; age equal to or above 65 years of age; non-institutionalized individuals; they give permission to be part of the study and if the participant presents with a clinical condition or comorbidity, it must be stable and enable participation in aquatic-based exercises classes as approved by local medical staff. The exclusion criteria are: individuals less than 65 years of age; individuals with medical diagnosed pathologies that jeopardize their health while preforming aquatic based exercises, participants that attend less than 50% of all the sessions and participants who cannot complete all of the proposed tests.

The participants will be distributed randomly into different exercise groups based on their registration for one of the schedules offered for the hydro-gymnastics sessions. There will be three distinct schedules (9.00, 9.50 and 10.40), with the constraint being that the participants must attend the same schedule for the whole year. The 9.00 session includes the continuous aerobic program, the 9.50 session includes the interval aerobic program, and the 10.40 session includes the combined exercise program. This information will not be provided to participants before they register for the sessions so it will not be possible to establish any association between the schedule and the different exercises programs. Such information will be communicated later in the study. The control group will be randomly recruited from the community and will include those individuals that have not been involved in any kind of physical exercise during the last year.

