Three physical exercise programs will be conducted for a time period of 28 weeks, two times per week (non-consecutive days) and have the following common characteristics: all sessions will have a duration of 45 min, taking into account previous studies [10] that suggest sessions of this duration seem to be sufficient to provide changes in several parameters in the elderly population; they will be aquatic-based (the water level will be between 0.80 and 1.20 m with a temperature of approximately 32 °C); and they will be conducted to the rhythm of music (bpm) that can be adjusted to achieve the target HR. Sessions are divided into three parts: the initial part, main part and final part, with common exercises in the initial and final part of the three programs. The initial part or warm-up has a duration of 10 min and the purpose is to assist participants to adapt to the water environment, more specifically, for participants’ to acclimatize and prepare for muscular and metabolic stimulation. Simple aquatic-based exercises will be conducted, e.g., displacement and isolated movements. The exercises increase in complexity and intensity during this initial phase. The final part has a duration of 5 min. This part will be divided into two phases: return to calm (relaxation) where relaxing exercises are conducted with the purpose of returning the participants’ heart rate (HR) value to a resting level. The second phase is composed of stretching routines that stretch the most exercised muscle groups stimulated in the main part of the session and reduce the level of lactic acid and the occurrence of post-exercise pain. The main part is different in the three physical exercise programs and their characteristics are described in Table 1. All physical exercise programs will be planned and implemented according to the recommendations of the American College of Sports Medicine [19] and conducted by specialized physical exercise technicians (with a degree in sports science) with specialization in hydro-gymnastics (instructor course—level 1).

HR monitors (Polar V800) will be used on the participants during all sessions of the different physical exercise program. The intensity of each exercise program will be monitored using the data provided by the Polar V800 and adjusted accordingly. As a precaution and safety measure, the intensity will be indirectly calculated using the following equation [20]:(1)Target HR=((Maximum HR−Resting HR) % intensity)+Resting HR

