## 3. Expected Results/Discussion

The main aim of this study is to assess the impact of different aquatic exercise programs (a continuous aerobic program, aerobic interval program and combined program) on risk markers of cardiometabolic diseases in older people. The study is guided by scientific-based evidence on the practice of physical exercise in the elderly population [11,36].

The practice of regular physical exercise is considered as the optimum tool in the prevention and treatment of various types of cardiometabolic diseases. Thus, it is important that research on this topic continues; by doing so, new intervention methods can be identified and their efficacy validated. The offer of aquatic physical exercise programs is highly successful among the elderly because they transform physical exercise into something more pleasant and suitable for this particular population. However, the high costs of maintaining aquatic environments and the additional difficulties associated with assessment methodologies and specific equipment needed to monitor exercise in aquatic environments, means this topic not yet been sufficiently explored in the literature.

After completion of the data collection and analysis, the participants in the experimental groups are expected to show positive developments with regard to the anthropometric level, physical function, the intima-media thickness of the carotid arteries, heart rate variability, cognitive function, mental health and a number of biochemical markers. It is also expected that statistically significant differences will be found between the exercise groups for some of the variables. In the control group, no changes are expected in the analyzed variables. It is believed that the expected results can be attributed to the physical and physiological effects of the aquatic environment associated with the different proposed exercise protocols. The results will be published after the study is completed.

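### Each programme is one class at one fixed hour, so its effect cannot be separated from class and time of day, and the planned tests ignore any class-level correlation

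*Protocol article*

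**What the plan says.** Section 2.2 (Participants) sets up the exercise arms by timetable: "There will be three distinct schedules (9.00, 9.50 and 10.40"). It then assigns one programme to each hour: "The 9.00 session includes the continuous aerobic program, the 9.50 session includes the interval aerobic program", "and the 10.40 session includes the combined exercise program". There is no crossing between hours, because "the participants must attend the same schedule for the whole year". Participants are to be "distributed randomly into different exercise groups based on their registration for one of the schedules offered".

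Section 2.1 (Design) gives one pool, two sessions a week of 45 minutes, and 28 weeks. Section 2.3 (Protocols) counts 56 sessions, which is 28 × 2 and so fits one class per programme. The article describes no second class of any programme and no rotation of programmes over hours.

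On staffing, section 2.3 says that the programmes are "conducted by specialized physical exercise technicians (with a degree in sports science) with specialization in hydro-gymnastics". It does not say who leads which session.

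Section 2.6 (Statistical Analysis) compares groups with the independent-samples t-test or the Mann–Whitney test, and names no allowance for class. Section 3 (Expected Results/Discussion) expects significant differences between exercise groups on some variables. It adds: "It is believed that the expected results can be attributed to the physical and physiological effects of the aquatic environment", and goes on to link this with the different exercise protocols.

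**The concern.** This point is separate from how participants come to be in a slot. Even perfect individual randomisation would balance only the people. It would not balance what happens to a class as a class.

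Anything specific to one session acts on everyone in that programme and on nobody in the other two. Examples are the hour of day, the group's cohesion and the way the session is run. The outcomes include well-being, self-esteem, depression and stress scales, which a group's atmosphere could plausibly move. Participants who attend fewer than half of the sessions are excluded, so a class's appeal can also affect who is analysed.

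Two things are at stake. First, a difference between programmes may be a difference between classes or hours. Second, the planned tests estimate their error from variation within classes only, so they understate the uncertainty of a comparison between programmes if classes vary. Comparing the programmes is part of the stated purpose of the trial.

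**Working it through.** **Structure.** There are three programmes, three hours and one class each (section 2.2). Each programme therefore has one cluster, which leaves 0 degrees of freedom for variation between classes within a programme. Programme, class and hour are fully aliased. More participants in the same class do not help: the effective number per programme is n/(1 + (n − 1) × ICC), which cannot exceed 1/ICC. That ceiling is 100 at ICC 0.01 and 20 at ICC 0.05.

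**Class size.** The article gives none, so two values are used, each assuming an equal split over four groups:
- The stated sample size is 76, and 76/4 = 19. The 76 reproduces as a repeated-measures within-between interaction with f = 0.25, 4 groups, 2 measures and alpha 0.05. Power is then 0.959, assuming a correlation of 0.5 between measures. That calculation contains no term for class.
- 102 people agreed to participate (section 2.2), and 102/4 = 25.5, taken as 25.

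**ICC.** No value is given in the documents. A range of 0.01 to 0.05 is assumed.

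**Formula.** With total variance 1, the true variance of a difference between two class means is 2 × (ICC + (1 − ICC)/n). The t-test estimates only the within-class part, 2 × (1 − ICC)/n. The ratio is

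R = (1 + (n − 1) × ICC)/(1 − ICC).

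The true two-sided error of a nominal 5% test is the probability that |t| exceeds t(0.975)/√R, on 2n − 2 degrees of freedom.

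| n per class | ICC | R | √R | t(0.975)/√R | True error |
|---|---|---|---|---|---|
| 19 | 0.01 | 1.18/0.99 = 1.19 | 1.09 | 2.028/1.09 = 1.86 | 7.1% |
| 19 | 0.02 | 1.36/0.98 = 1.39 | 1.18 | 2.028/1.18 = 1.72 | 9.4% |
| 19 | 0.05 | 1.90/0.95 = 2.00 | 1.41 | 2.028/1.41 = 1.43 | 16.0% |
| 25 | 0.01 | 1.24/0.99 = 1.25 | 1.12 | 2.011/1.12 = 1.80 | 7.9% |
| 25 | 0.02 | 1.48/0.98 = 1.51 | 1.23 | 2.011/1.23 = 1.64 | 10.8% |
| 25 | 0.05 | 2.20/0.95 = 2.32 | 1.52 | 2.011/1.52 = 1.32 | 19.3% |

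With the normal value 1.96 in place of t, the two ends at 25 per class are 8.0% and 19.8%. The effective number per programme falls from 19 to between 16.1 and 10.0, or from 25 to between 20.2 and 11.4.

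These figures are for one programme against another. The control group attends no class, so only one side of a programme-versus-control comparison is clustered. The programme's estimated effect there still includes its single class and hour.

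**The case against.** The strongest reply is that delivery is largely standardised. Section 2.3 gives all three programmes the same length, warm-up, final part, water conditions and instructor qualifications. Heart-rate monitors are worn in every session, and intensity and music tempo are adjusted towards a target. Table 1 sets the content and intensity bands of the main part. This stands as mitigation: it narrows the route by which a class could alter the exercise dose. It does not replicate the class, and it does not reach the hour of day or the group's social effect.

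A second reply is that the ICC is unknown and probably differs between carotid thickness, cytokines and questionnaires. This also stands. A reader might infer that the planned p-values are certainly too small, but that holds only if the ICC is above zero. The table shows a range under an assumption, not an estimate for this trial.

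A reader might also infer that each programme has its own instructor, so that a better teacher would appear as a better programme. The article does not support that. It speaks only of technicians in the plural, and three consecutive sessions in one pool could be led by one person or a rotating team. A condensed article may well leave the teaching rota to the full protocol, so its absence is not a fault.

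The five minutes between sessions (50 − 45) might be read as a further disadvantage for the later classes. Every class is planned at the full 45 minutes, and nothing in the article suggests an effect.

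Finally, the attribution in section 3 is hedged and concerns expected results. It is not a planned causal conclusion, but it does indicate how differences would be read.

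**Conclusion.** The point holds for class and time of day, from what the article itself states. It holds for the instructor only if each session has its own technician, which is not stated. No sample size and no later model can separate programme from class with one class per programme.

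The effect on the tests is conditional. At an assumed ICC of 0.01 to 0.05, a nominal 5% error for one programme against another becomes about 7% to 16% at 19 per class and about 8% to 20% at 25 per class. At an ICC of zero there is no inflation, although the aliasing with hour of day remains. The class sizes rest on an equal four-way split.

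The arrangement does not invalidate the trial. It limits the claim: a difference between two programmes is a difference between two programmes as delivered in their classes and hours.

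**What to change.** - **Section 2.6:** add a sensitivity analysis for each comparison between programmes that multiplies the standard error by √R at ICC 0.01, 0.02 and 0.05, using the class sizes actually analysed. On the figures above, the multiplier runs from 1.09 to 1.41 at 19 per class and from 1.12 to 1.52 at 25. Report whether the conclusion survives.
- **Section 3:** present differences between programmes as exploratory, and as effects of each programme as delivered in its class and hour, not of the exercise protocol alone. State that class and hour cannot be separated from programme.
- **Section 2.3:** state who leads the sessions. If different technicians lead the three sessions, rotate them equally over the programmes and record the technician for each session in the attendance database. This deals with the instructor only; class and hour stay aliased.

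The first two changes cost a short calculation and a few sentences, and make the conclusions more cautious. A rota, if needed, requires technicians to learn all three session plans and adds one column to the database.

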## Abstract

Cardiometabolic diseases are one of the primary causes of mortality and morbidity worldwide and sedentary lifestyles are contributing factors to these pathologies. Physical exercise has been recognized as an important tool in the prevention and treatment of these diseases. However, there are still some doubts about the efficacy of certain type of physical exercise programs for older participants. The main goal of this study is to assess the impact of different aquatic-based physical exercise programs on risk markers of cardiometabolic diseases in older people. The study group will consist of non-institutionalized individuals, within the age group of 65 or older. The sample will be randomly divided into four groups, three experimental groups (EG) and one control group (CG). Participants from the EGs will be exposed to three physical aquatic-based exercise programs for a period of 28 weeks (continuous aerobic, interval aerobic and combined). The evaluated parameters include anthropometry, physical functions, mental health, cognitive function, carotid arteries intima-media thickness, heart rate variability and biochemical markers. The results will allow an interpretation of the impact of different aquatic-based physical exercise programs on cardiometabolic diseases markers and can also be used as a tool for professionals to prescribe adequate and more efficient physical exercise programs.

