*Maximum HR* is calculated with the following equation for senior populations [21]:(2)Maximum HR=207−(0.7×age)

The control group consists of non-institutionalized individual participants who have not partaken in any physical exercise during the preceding year. These participants will be encouraged to conduct their daily activities as usual, except for the data collection (M1 and M2) organized by the researchers.

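### The exercise-versus-control comparison is not randomised, and only controls must have been inactive for a year, yet the planned group tests are unadjusted

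*Protocol article*

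**What the plan says.** The Abstract gives this account of allocation: "The sample will be randomly divided into four groups, three experimental groups (EG) and one control group (CG"). Section 2.1 likewise labels the study randomised.

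Section 2.2 gives another account. Exercise participants are "distributed randomly into different exercise groups based on their registration for one of the schedules offered for the hydro-gymnastics sessions". Of the three slots, each belongs to one exercise programme, and none leads to the control group. Controls come in by a further step. They are drawn from the community, and their group "will include those individuals that have not been involved in any kind of physical exercise during the last year". Section 2.3 repeats the requirement, describing controls as "non-institutionalized individual participants who have not partaken in any physical exercise during the preceding year".

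The common inclusion criteria in section 2.2 begin with "individual of both genders; age equal to or above 65 years of age; non-institutionalized individuals; they give permission to be part of the study"; a condition on stable comorbidity follows. Neither these nor the exclusion criteria mention earlier physical activity.

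For comparisons between groups, section 2.6 plans the independent-samples t-test, or the Mann–Whitney U test where data are not normal. Neither uses the M1 value or any other covariate.

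**The concern.** The expectation in section 3 is that the exercise groups improve and the controls do not change. That contrast supports a causal claim only if the two sides were comparable at the start, or if the analysis deals with the fact that they were not.

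Here a person who exercised last year may join an exercise group but can never be a control. Exercise participants have also chosen to sign up for a class. Prior activity and willingness to attend classes are plausibly related to fitness, body composition, blood pressure, heart rate variability and mood, all of which are measured as outcomes. With an unadjusted test, a difference present before the programmes began passes straight into the result. The randomised label would then tell readers that such a difference can only be due to chance.

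**Working it through.** **Step 1: compare the two accounts of allocation.**

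| Feature | Abstract and section 2.1 | Sections 2.2 and 2.3 |
|---|---|---|
| Source of controls | Same sample as the exercise groups | Recruited separately from the community |
| Assignment to exercise or control | Random | No random assignment described |
| Prior-activity rule | None stated | None for exercise participants; no exercise for a year for controls |

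The word 'randomly' applied to control recruitment in section 2.2 describes how people are found, not how they are assigned. The same section also says "The sample was recruited by the non-probabilistic method for convenience". Nothing in the document describes chance deciding between exercise and control, so the two accounts cannot both be right.

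**Step 2: what follows with certainty.** The route of entry and the eligibility rule differ between the two sides. That is a property of the design. How far the enrolled groups actually differ is not stated and cannot be worked out from the document.

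**Step 3: illustrate how the planned test responds.** There is no figure in the plan to reproduce on this point. The inputs are therefore assumptions, except the 5% level from section 2.6:
- no true programme effect;
- a two-sided 5% t-test of M2 values, one exercise group against control;
- a difference of *d* SD at M2 due to selection alone;
- 25 per group, from 102/4 = 25.5 rounded down. The document gives no group sizes and does not say whether the 102 who agreed include the controls. As a second case, 19 per group, from the planned total of 76/4.

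The test statistic follows a noncentral t distribution with 2n − 2 degrees of freedom and noncentrality d / √(2/n). The rejection rate is the probability that it falls outside the two-sided 5% critical values.

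For n = 25, √(2/25) = 0.283, so d = 0.5 gives noncentrality 0.5/0.283 = 1.77 on 48 degrees of freedom. The results are:

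| Selection difference at M2 | 25 per group | 19 per group |
|---|---|---|
| 0.1 SD | 6.4% | 6.0% |
| 0.2 SD | 10.7% | 9.2% |
| 0.3 SD | 18.0% | 14.7% |
| 0.5 SD | 41.0% | 32.3% |

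All exceed the nominal 5%. The difference *d* is placed directly at M2. It is not an M1 gap multiplied by the M1–M2 correlation, because that shrinkage suits a chance imbalance within one population, whereas a stable difference between two populations would persist.

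**Step 4: what adjustment for M1 would achieve.** If the same gap *d* is present at M1 and M2, with equal SDs and within-group correlation ρ, an ANCOVA leaves d − ρd = d(1 − ρ). With d = 0.5 and assumed ρ of 0.5 or 0.8, this is 0.5 × 0.5 = 0.25 SD or 0.5 × 0.2 = 0.10 SD. The bias is smaller but still present.

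**The case against.** Four arguments on the other side deserve weight.

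- **Baseline values are collected.** Section 2.1 has every outcome measured at M1 as well as M2, so baseline adjustment is possible with data already planned. This stands. A reader might infer from the list of survey items in section 2.4.1, which does not name prior exercise, that the imbalance could never be adjusted for. The document does not support that: the list is condensed, the form itself is not shown, and controls must be asked about prior exercise somewhere in order to qualify. What stands against the plan is that section 2.6 specifies unadjusted tests.
- **The exercise participants may be inactive too.** This is possible. Section 2.2 says that 150 people from the community were personally invited, so nothing shows that they already attended classes. But nothing requires inactivity of them either.
- **The direction is open.** A reader might infer that the bias must favour exercise. Fitter entrants could look better at M2 and yet have less room to improve, so the direction may depend on the outcome and on whether M2 values or changes are compared. The document does not settle it.
- **The paired M1–M2 tests take account of baseline.** They do so within a group. They do not compare exercise with control, so they do not repair that contrast.

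An analysis plan that is not shown might add adjustment. It could not turn separate recruitment under different rules into random assignment.

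**Conclusion.** The point holds as a contradiction and a design weakness. The Abstract and section 2.1 claim random allocation to four groups. Sections 2.2 and 2.3 describe a separately recruited control group with an extra eligibility rule. The exercise-versus-control comparison is therefore non-randomised, and the unadjusted tests leave it exposed to selection.

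The rates in the table show how sensitive the planned test is. They are not an estimate of bias in this trial, because they rest on assumed group sizes and assumed differences. It would be wrong to read 41% as the expected false-positive rate.

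The scope is limited to exercise versus control. Comparisons among the three programmes do not involve the control group and are not affected by this point.

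**What to change.** **If allocation is still open:** apply one prior-activity criterion to everyone, and randomly assign consenting participants from a single pool to all four groups, including control. Applying the control group's rule to everyone may exclude some current exercisers. Section 2.2 reports recruitment in the past tense, so this option may no longer be available.

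**Otherwise:**
1. Correct the Abstract and section 2.1 to say that the exercise-versus-control comparison is non-randomised, in line with sections 2.2 and 2.3.
2. Record prior-year exercise (type and hours per week) for all participants at M1.
3. In section 2.6, replace the unadjusted between-group test with an analysis of M2 adjusted for the M1 value, for example ANCOVA.
4. Add an analysis restricted to previously inactive participants. All controls have no prior exercise, so covariate adjustment alone would extrapolate for those who do.
5. State that adjustment for M1 reduces selection bias but does not remove it.

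The cost of this second route is one or two survey questions, a little more analysis, a smaller sample in the restricted analysis and a weaker design label.
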